# The clinical evaluation of electroacupuncture combined with mindfulness meditation for overweight and obesity: study protocol for a randomized sham-controlled clinical trial

**DOI:** 10.1186/s13063-022-06725-8

**Published:** 2022-09-27

**Keywords:** Obesity, Overweight, Acupuncture, Electroacupuncture, Mindfulness meditation, Mindfulness intervention, Evidence-based Chinese medicine

## Abstract

**Background:**

Overweight and obesity have reached an epidemic level which impacts individual health and creates a financial burden worldwide. Evidence has shown that electroacupuncture is effective for weight loss when combined with lifestyle intervention, while mindfulness meditation can enhance the outcome of weight loss programs. This study aims to evaluate the safety and the add-on effect of electroacupuncture and mindfulness meditation for weight management in overweight and obesity.

**Methods/design:**

This is a sham-controlled, three-armed randomized clinical trial. A total of 165 participants with BMI between 25 and 39.99 and aged between 18 and 60 who meet the inclusion and exclusion criteria will be randomized into [1] electroacupuncture plus mindfulness meditation group, [2] sham electroacupuncture plus mindfulness meditation group, and [3] electroacupuncture only group. The total duration of this study will be 22 weeks, which consists of a 2-week run-in period, a 12-week intervention period, and an 8-week follow-up period. Participants will receive 12 weekly treatments during the intervention period. Primary outcomes will include body mass index, waist and hip ratio, and body composition. Secondary outcomes will be measured by the Weight-Related Symptom Measure, Obesity and Weight Loss Quality of Life, the Power of Food Scale, and the Chinese medicine differential diagnosis questionnaire. Outcomes will be assessed at the baseline, and endpoints of the 3rd, 6th, 9th, 12th, 14th, 16th, and 20th week.

**Discussion:**

This clinical trial will investigate the add-on effect of two combined interventions for weight loss treatment. The findings of this study may contribute to the development of a cost-effective and multidisciplinary weight management approach.

**Trial registration:**

Australia and New Zealand Clinical Trials Registry (ANZCTR) ACTRN12618000964213. Registered on 07 June 2018.

**Supplementary Information:**

The online version contains supplementary material available at 10.1186/s13063-022-06725-8.

## Background

Obesity and overweight are defined as the excessive accumulation of fat in the body which impairs health [1]. Body mass index (BMI) is an indicative tool to estimate the amount of fat deposited in the body. Individuals who have a BMI equal to or above 25 are classified as overweight and obese if their BMI is equal to or above 30 [2].

The worldwide prevalence of overweight and obesity has almost tripled since 1975 [1]. Research has shown that overweight and obesity are linked to various chronic conditions such as cardiovascular diseases, type II diabetes mellitus, hypertension, various types of cancers, gynaecological issues and osteoarthritis [3, 4]. Due to social stigmatization, overweight and obese individuals often suffer from body dissatisfaction, anxiety, depression, lowered self-esteem, and disorders of eating behaviours [5, 6]. These impacts can often lead to increased indirect costs to healthcare and government welfare expenditure and indirect costs such as loss of work productivity [7].

Current weight management includes pharmacotherapy, dietary changes, physical exercise, bariatric surgery and behavioural changes [8, 9]. The cause of overweight and obesity is multifactored, including genetic, physiological, behavioural, sociocultural and psychological influences [10]. Therefore, the Australian clinical practice guidelines for the management of obesity suggest multicomponent lifestyle intervention for weight management, which includes diet changes, increased physical activities and behaviour changes to adopt a healthy lifestyle. Moreover, it is recommended that psychological interventions may improve weight management outcomes [11].

Dietary changes include a low-calorie diet which aims to decrease energy intake to facilitate weight loss [9]. On the other hand, physical exercise increases energy expenditure which can result in weight reduction [12]. However, decreased food intake can cause an increase in hunger sensation and decreased satiety [13]. An increase in the level of physical exercise also induces muscle pain [14]. All these factors may contribute to psychological distress and decrease the tendency to sustain these changes.

Consumption of pharmacological anti-obesity treatment may cause disturbing side effects such as faecal incontinence and deficiency in fat-soluble vitamins [15]. Bariatric surgeries can significantly decrease body weight. However, it may lead to death or complications, such as acid reflux, malnutrition, and bleeding [16, 17].

Acupuncture is considered a type of complementary and alternative medicine [18]. The traditional manual acupuncture treatment involves inserting fine needles into specific acupuncture points on the human body to treat various conditions [19]. Variants of acupuncture have also been developed, such as Electroacupuncture (EA), catgut-embedding and auricular acupuncture [20]. A recent systematic review evaluated the weight management outcome between variants of acupuncture. However, no conclusion has been drawn [20]. EA is one of the variants of acupuncture, which involves connecting two needling sites to an electro-stimulator to allow a predefined intensity of current to pass through the body in a constant pattern. Therefore it is a reproducible stimulation that can be applied in different clinical settings and has gained popularity to be used in research studies [21, 22].

Some studies found that EA reduced more weight than exercise [23, 24] and diet restriction [25]. Guo et al. [26] suggested that EA in combination with diet restriction may produce more weight loss than diet alone [11]. Three other studies have found that EA plus diet and exercise may reduce BMI more than diet and exercise alone [27–29]. Several studies also found that EA significantly reduced weight and BMI in comparison to sham EA [25, 30, 31]. Moreover, Li et al. [32] suggested that acupuncture combined with a diet therapy can be more effective than diet therapy alone. Animal studies indicated that EA can facilitate weight loss through modulating neurotransmitters to suppress appetite [33], promote browning of the white adipose tissue [34] and regulate gut flora [35].

Previous systematic reviews have investigated the effect of acupuncture on improving weight loss in obese people [32, 36–45]. Two systematic reviews suggested that acupuncture can have a positive effect on waist circumference (WC) and hip circumference (HC), reducing the WC by 2.02cm (95%CI 0.21 to 3.83, *p*=0.03) and WC by 2.74cm (95%CI 1.21 to 4.27, *p*=0.0004) [44, 45]. Kim, Trinh [24] reported that acupuncture combined with exercise is more effective than e exercise alone in reducing BMI (Hedges’ *g* = 1.104, 95%CI 0.531 to 1.678) [10]. Chen et al. [46] and our previous research suggested that the mechanism of acupuncture for weight loss may be due to reducing excessive appetite and increasing metabolism [17, 20]. A systematic review on RCT of acupuncture for obesity suggested that acupuncture may lower serum leptin levels in obese adults [47].

Even though there is increasing evidence supporting the use of acupuncture for overweight and obesity [21], the current Australian clinical guidelines for obesity do not include acupuncture as a modality for treatment. Therefore, further investigations are needed to provide more evidence to assist clinical decisions.

Mindfulness meditation (MM) is a psychological approach with increasing popularity for weight management [48]. The term mindfulness is a concept that originated from Buddhist traditions. Mindfulness is defined as the awareness of paying attention to the current moment without judgment to the thought [49]. It has been further defined that mindfulness also involves in sustaining attention through self-regulation [50] and that the current moment should be experienced with an acceptance attitude [51].

A recent systematic review suggested that MM can be effective in improving eating behaviour such as emotional eating and binge eating and can be used in conjunction with other interventions for weight loss treatment [48]. Studies have found that better weight loss outcomes and eating behaviours have been achieved by adding MM to a standard behaviour weight loss program [48, 52].

There is evidence supporting that EA can enhance the outcome of diet and exercise for weight loss [37, 38], and MM can enhance the weight management outcome by improving eating behaviour [48]. However, the combination of EA and MM has never been investigated.

This clinical trial aims to clinically evaluate the add-on effect of MM to EA and vice versa for people with overweight or obesity.

## Methods

### Trial design

This is a sham-controlled, three-arm randomized superiority clinical trial designed in accordance with the Guideline of National Statement on Ethical Conduct in Human Research 2007 (Updated July 2018) [53]. This clinical trial will be conducted in the Chinese Medicine Research Laboratory at the Royal Melbourne Institute of Technology (RMIT) University Bundoora West and Melbourne city campus. The total duration of this trial will be 22 weeks, which consists of a 2-week run-in period, a 12-week intervention period, and an 8-week follow-up period. Figure 1 shows the flow chart of the clinical trial procedure. The Standard Protocol Items: Recommendations for Interventional Trials (SPIRIT) Checklist and figure are provided in the Additional file 1 and Fig. 2, respectively [54].

**Fig. 1 Fig1:**
[figure not shown]
Flow chart for clinical trial procedure

**Fig. 2 Fig2:**
[figure not shown]
The SPIRIT study schedule

### Registration and ethics approval

This study protocol has been developed in accordance with the revised Standards for Reporting Interventions in Clinical Trials of Acupuncture (STRICTA) [55] and the Consolidated Standard of Reporting Trials (CONSORT) guidelines [56]. The RMIT University Human Research Ethics Committee (HERC) has approved this trial protocol with project number 21457. This trial has been registered with the Australian New Zealand Clinical Trial Registry (ACTRN1261800064213).

### Participants

Overweight and obese adult volunteers will be recruited for this study. Participants will be screened according to the following inclusion and exclusion criteria:

### Inclusion criteria

Eligible participants must fulfil the following criteria:Being overweight or obese, with BMI between 25 and 39.99 inclusively;Adult aged between 18 and 60;Be available during the period of this clinical trial; andGive written consent to participate in the study

### Exclusion criteria

Participants will be excluded if they have one or more of the following conditions:Serious chronic medical conditions, such as cardiovascular diseases, cancer, HIV, and epilepsy;Women who are pregnant or lactating;Drug-induced secondary obesity;Medical conditions which are known to link with obesity, such as uncontrolled high blood pressure, polycystic ovary syndrome, hypothyroidism, Cushing syndrome, and Hashimoto’s disease;Mental conditions such as clinical depression, anxiety, PTSD, and psychosis;Participants who are not willing to be treated by acupuncture or to practice meditation;Difficulties with understanding and reading English;Taking blood-thinning medications;Auditory impairment who cannot listen to audio records; andParticipants who received treatment for obesity in the past 3 months, including medical treatment or participated in weight loss programs.

### Sample size

The sample size was calculated based on a previous study comparing the acupuncture group with the sham acupuncture for BMI [57]. After the treatment, the effect size estimate was 0.56. The sample required to achieve 80 per cent power at a significance level of 5% is 55 per group (total *n* = 165).

### Recruitment and screening

All prospective participants will receive a link to two online Microsoft forms, which include the Participant Information and Consent Form (PICF) (Additional file 2) and The General Information and Screening Questionnaires (GISQ). They will be asked to thoroughly read the PICF, and electronically submit the GISQ if they are willing to participate in the trial. The research team will review all GISQ to screen for eligible participants. A screening interview will be scheduled to collect all baseline measurements, ensuring that all participants comply with the selection criteria. Participants who meet the inclusion criteria will be recruited for this clinical trial. The investigators will be responsible for obtaining written consent from the participants before randomization.

### Randomization

Participants will be randomly assigned into three groups. An independent statistician will be responsible for generating a randomization code by using a computer program with a 1:1:1 allocation. The code will be placed into individually sealed opaque envelopes, which contain information about the allocated treatment group. All participants will select their envelope from the available envelopes and hand them over to the researcher. The researcher will ensure that the envelope will not be opened until the name of the allocated participants is written on the envelope. Group assignments will not be changed after the allocation has been made.

### Blinding

The acupuncturist and the researcher who is responsible for playing pre-recorded mindfulness meditation audio records will not be blinded. A research assistant who is responsible for entering outcome measurements is blinded to treatment allocation. The treatment allocation will be blinded to an individual data manager, who is responsible for manually entering information to a securely stored database. To ensure allocation concealment, any discussion between the treatment provider and the participant is required to be kept minimal.

### Interventions

#### Electroacupuncture (EA)

The intervention consists of 12 weekly sessions, and each session includes EA treatment with 30 mins needles stimulation. The acupuncture points are Zusanli (ST36), Sanyinjiao (SP6), Tianshu (ST25), Zhongwan (CV12), Fenglong (ST40), Guanyuan (CV4), Qihai (CV6), and Yinlingquan (SP9). The location of the acupuncture points will follow the standard point location in the Western Pacific region published by WHO [58]. Figure 3 below illustrates the location of the acupuncture points for EA treatments.

**Fig. 3 Fig3:**
[figure not shown]
The acupuncture points for EA treatment

Sterilized stainless-steel single-use disposable needles (0.25 × 40mm; Seirin, Seirin Corporation, Japan) and electro-stimulator (ES-160; ITO, ITO Company Ltd., Japan) will be in this trial. Skin sterilization will be performed by applying 70% isopropyl alcohol swab to the area. All acupuncture points will be needled perpendicularly with a guide tube. Insertion depth will be approximately 25 mm, depending on the location of individual points. Each point will be connected to the electro-stimulator with fast and slow modes with frequency switching between 33 − 100 Hz at 48 mA peak intensity, and the connections are shown in Table 1. All needles will be removed after 30 min of electro-stimulation.

**Table 1 Tab1:** Connection of needles to electro-stimulator

Anode (red)	Cathode (black)
CV 12	ST 25 (left)
CV 6	ST 25 (right)
SP 6	SP 9
ST 36	ST40

The acupuncturist who is providing acupuncture treatment in this trial is a registered acupuncturist under AHPRA (Australian Health Practitioner Regulation Agency) as a qualified acupuncturist for more than 3 years of clinical experience.

#### Sham electroacupuncture (SEA)

The SEA also consists of 12 weekly sessions, and this is penetrating acupuncture on non-acupuncture points (1 cm away from the acupuncture point and meridian). The same type of acupuncture needles will be used for SEA with the exact skin sterilization method. All acupuncture points will be needled perpendicularly with a guide tube. Insertion depth will be approximately 25 mm, depending on the location of individual points. Each point will be connected to a sham electro-stimulator (showing a continuous wave at a frequency of 30 Hz but without actual stimulation). All needles will be removed after 30 min of needle retention.

#### Mindfulness meditation

The mindfulness meditation (MM) intervention will involve practising a 10-minute pre-recorded MM during 12 weekly sessions. The MM was adapted from Mindfulness-Based Eating Awareness Training (MB-EAT) developed by Jean Kristeller [59]. It is a sitting meditation to be practised in individual settings, which requires participants to focus on their awareness through breathing.

At the initial session, a copy of the pre-recorded MM audio file will be sent to the ‘participants’ email for daily self-practice. The participants will also receive a copy of the MM information and instruction booklet, which explains the procedure of practising mindfulness meditation. Participants will need to practice daily at home for 10 min, following the instruction by listening to the playback of the MM audio file.

Email reminders will be sent to the participants for appointments to improve adherence to intervention protocols. A log book will be provided to record the frequency and duration of each MM self-practice.

### Group design

This is a three-arm clinical trial, which consists of the EA plus MM group (EAM), SEA plus MM group (SAM) and EA only group (EAO). Participants will be asked to continue with their usual diet and exercise, and refrain from participating in any weight loss program or consuming any weight loss supplements/medications, otherwise will be considered as a dropout during the study. The description of each group is listed below (Table 2):

**Table 2 Tab2:** Group description

Group	Description
Electroacupuncture + MM (EAM)	This group consists of a combination of EA and mindfulness meditation interventions. Participants will be given the abovementioned EA treatment. They will then be prompted to follow the 10 min pre-recorded MM instruction. They will be instructed to practice MM daily.
Sham electroacupuncture + MM (SAM)	This group consists of a combination of EA and mindfulness meditation interventions. Participants will be given the abovementioned sham EA treatment. They will then be prompted to follow the 10 min pre-recorded MM instruction. They will be instructed to practice MM daily.
Electroacupuncture only (EAO)	This group consists of the abovementioned electroacupuncture treatment only.

*Abbreviations*: *MM* Mindfulness meditation, *EA* Electro-acupuncture

The add-on effect of MM to EA comparing the treatment group (EAM) with the control group (SAM). On the other hand, to assess the add-on effect of electroacupuncture on mindfulness meditation, the treatment group (EAM) will be compared with the control group (EAO).

Participants will confirm their next appointment during their visits, and a message will be sent to the participants to remind and confirm their weekly visits.

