## Discussion

Overweight and obesity have reached an epidemic level across the world over the past decades [1]. More effective weight management strategies are urgently needed to reduce the prevalence and impacts on our society. Due to the multifactorial cause of overweight and obesity, interventions that only target one single factor may not achieve a satisfying weight management outcome [60–62].

Evidence has shown that acupuncture is effective in weight management when it is being used alone or combined with other weight loss interviews to enhance weight loss outcomes [32, 38, 40]. EA is a variant of acupuncture with a replicable mode of stimulation that enables consistent stimulation throughout treatment sessions [21]. Additionally, other evidence has suggested that mindfulness meditation may be added to weight loss programs to enhance the treatment results [52]. Furthermore, the clinical practice guidelines for the management of overweight and obesity in adults, adolescents and children in Australia suggest that psychological component can be added to weight loss programs to increase the likelihood of success [11]. To our best knowledge, this is the first trial protocol evaluating the effect and safety of EA combined with mindfulness meditation for weight management.

The aim of this RCT is to evaluate the add-on effect of EA and MM on weight loss. In terms of group design, the add-on effect of EA will be evaluated by comparing the EAM group and SAM group. The add-on effect of MM will be assessed by comparing the EAM group and the EAO group. This design has put a limitation on this trial in which we cannot blind the participants for the EAO group who will not be participating in the MM component. Participants in the EAM and SAM groups will be blinded by sham electroacupuncture treatment. The SA method was designed as penetrating insertion to a non-acupuncture point, all acupuncturists will receive training on needling to the predefined non-acupuncture points to ensure consistency of point location for the SAM group. The wire of the electro-stimulator will be modified to stop the current being flow to the body; this ensures that the SAM group participants receive no electro-stimulations at all. Participants will be told that the intensity of stimulation is predefined, and therefore they may or may not be able to feel for the stimulation.

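### Group design swaps the comparators for the two add-on effects and contradicts the Discussion, so each result would be credited to the wrong therapy

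*Protocol article*

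**What the plan says.** The protocol article defines the arms in Methods, Group design: the trial "consists of the EA plus MM group (EAM), SEA plus MM group (SAM) and EA only group (EAO"). Table 2 confirms the two control arms. For SAM, "Participants will be given the abovementioned sham EA treatment"; for EAO, "This group consists of the abovementioned electroacupuncture treatment only".

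The text after Table 2 then ties each add-on question to a comparison:

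- MM: "The add-on effect of MM to EA comparing the treatment group (EAM) with the control group (SAM").
- EA: "to assess the add-on effect of electroacupuncture on mindfulness meditation, the treatment group (EAM) will be compared with the control group (EAO").

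The Discussion ties them the other way round:

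- EA: "the add-on effect of EA will be evaluated by comparing the EAM group and SAM group".
- MM: "The add-on effect of MM will be assessed by comparing the EAM group and the EAO group".

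The Statistical analysis section plans ANCOVA on BMI and WHR for differences between groups at the end of treatment and of follow-up. It does not say which pair of arms answers which question.

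The SAM row of Table 2 opens with "This group consists of a combination of EA and mindfulness meditation interventions". The EAM row opens with the same sentence, where it is correct.

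**The concern.** A comparison can show what a component adds only if one arm has that component and the other does not. The Methods propose to measure what MM adds by comparing two arms that both receive MM, and what EA adds by comparing two arms that both receive EA. Neither comparison can do that. The article also publishes two opposite definitions of the same contrasts.

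The closing sentence of the Background gives the aim as evaluating what MM adds to EA and what EA adds to MM, so these contrasts carry the main efficacy objective. An analyst who followed the Methods to the letter would report an EA result as an MM result and the reverse. A team that reported by the Discussion would be right, but would appear to depart from its own Methods.

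**Working it through.** The mapping can be settled from the arm definitions without any figure from the plan.

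**Step 1. Code the arms as (EA, MM), with sham EA as 0.**

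| Arm | EA | MM | Source |
|---|---|---|---|
| EAM | 1 | 1 | Group design, Table 2 |
| SAM | 0 | 1 | Group design, Table 2; Sham electroacupuncture section |
| EAO | 1 | 0 | Group design, Table 2 |

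**Step 2. Subtract.**

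- EAM − SAM = (1,1) − (0,1) = (1,0): EA changes, MM is held fixed.
- EAM − EAO = (1,1) − (1,0) = (0,1): MM changes, EA is held fixed.

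**Step 3. Check that an interaction does not rescue the Methods wording.** Let the mean outcome be μ + α·EA + β·MM + γ·EA·MM. Then EAM = μ + α + β + γ, SAM = μ + β and EAO = μ + α, so:

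- EAM − SAM = α + γ, which is what EA adds when MM is present.
- EAM − EAO = β + γ, which is what MM adds when EA is present.

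These are the two add-on effects in the ordinary sense, and they fall on the comparators named in the Discussion.

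**Step 4. Set the texts side by side.**

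| Question | Group design | Discussion | Arm definitions |
|---|---|---|---|
| What EA adds to MM | EAM vs EAO | EAM vs SAM | EAM vs SAM |
| What MM adds to EA | EAM vs SAM | EAM vs EAO | EAM vs EAO |

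Both rows of Group design are reversed, so one mistyped acronym does not explain it.

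**Step 5. Illustrate the consequence.** The inputs are an effect size of 0.56 and 55 per group (Sample size) and two-tailed tests at 5% (Statistical analysis). Two assumptions are added: EA truly has that effect, and MM adds nothing when EA is present (β + γ = 0).

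- Noncentrality for EAM vs SAM: 0.56 × √(55/2) = 0.56 × 5.244 = 2.94.
- Power by the normal approximation: Φ(2.94 − 1.96) ≈ 0.836. By the two-sample t-test: 0.829. Group design would label this significant result an MM effect.
- EAM vs EAO has a true difference of zero, so it is non-significant with probability 1 − 0.05 = 0.95. Group design would label this an absence of EA effect.

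**Context on the sample size.** An effect of 0.56 with 80% power at two-sided 5% needs 51 per group by the normal approximation or 52 by the t-test, against 55 stated. The plan is slightly conservative here, and the point does not depend on it.

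**The case against.** The strongest reply is that this is a drafting slip which the document itself resolves. The arms are named without ambiguity, the Discussion gives the correct mapping in full, and the first of the two sentences in Group design is grammatically incomplete, which suggests careless editing more than a chosen analysis. The same two pairwise comparisons are run under either mapping, so randomization, data collection, sample size and every numerical result are unchanged. All of this stands. It does not make the Methods text harmless, because no other part of the Methods links comparison to question, and the Methods are where a reader looks for the prespecified analysis.

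The 83% and 95% figures are also open to challenge. They are ordinary power and one minus alpha with the labels exchanged. They become probabilities of a wrong conclusion only if the analyst follows Group design literally. They assume one endpoint, an unadjusted t-test and no MM effect, whereas the plan is for ANCOVA on two outcomes at two times. That stands: they illustrate the consequence and do not estimate how likely the mistake is. If both components truly worked, or neither did, the swap might leave the significance statements alone and misattribute only the estimates.

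Three smaller points also stand:

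- The contrasts are not the whole objective, since the Abstract names safety as well.
- Neither contrast is a pure component effect. EAM vs SAM measures EA relative to penetrating needling away from the points without current. EAM vs EAO is not blinded to participants, as the Discussion concedes.
- The Table 2 wording is minor, because the row heading and the next sentence both say sham.

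**Conclusion.** The concern holds. Both contrast sentences in Group design are the reverse of what the arm definitions allow, and they contradict the Discussion. This follows from the definitions alone and needs no assumption about effect sizes. The error is confined to attribution: no arm, measurement, test or sample size is affected. It matters because it concerns the main efficacy questions. If EA worked as planned and MM added nothing, literal use of the Methods would credit MM with an effect about 83% of the time and find no significant EA effect about 95% of the time, under the single-endpoint, unadjusted t-test assumptions above. It should be corrected before analysis.

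**What to change.** In Group design, replace the two contrast sentences with: the add-on effect of EA is assessed by EAM versus SAM, and the add-on effect of MM is assessed by EAM versus EAO. This matches the Discussion, which needs no change. In Table 2, change the opening of the SAM row to a combination of sham EA and mindfulness meditation. If the full protocol or a statistical analysis plan carries the same sentences, correct them there too, and date the correction so that it is on record before results are seen.

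The cost is one paragraph and one table cell, with no effect on conduct, data or sample size. The article reports recruitment still in progress and plans no interim analysis, so on its own account the correction can precede any results.
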